### Who will take informed consent? {32a}

Written informed consent will be obtained from all participants. Given the emergency setting, if a participant lacks the capacity to provide consent owing to impaired consciousness or cognitive dysfunction, written informed consent will be obtained from a legally authorized representative (e.g., spouse, parent, or adult child). If the participant regains capacity, they will be informed about the study, and their consent for continued participation will be obtained. To ensure privacy, all personal information will be pseudonymized using participant ID codes.

### Additional consent provisions for collection and use of participant data and biological specimens {32b}

The link between the ID codes and identifiable personal information will be stored in a secure, locked location at the study site. Access to the raw data will be restricted to authorized study personnel only. All data will be maintained in accordance with the CRA and the study protocol.

## Intervention and comparator

### Intervention and comparator description {15a}

The intervention period will be 3 days. The detailed protocols for the study medications are summarized in Table 1 and Fig. 1.

**Table 1 Tab1:** Protocol for study medications in the Active and Passive PBPM groups

Group	Route	Scheduled medication(19:00)	Action on insomnia
Active PBPM	Oral	**Ramelteon** 8 mg + **lemborexant** 5 mg	Additional **lemborexant** 5 mg (if insomnia persists)
	Non-oral	**Blonanserin** **patch** 20 mg (19:00–06:00)	**Hydroxyzine** (rescue)
Passive PBPM	Oral	None	1. **Ramelteon** 8 mg + **lemborexant** 5 mg 2. Additional **lemborexant** 5 mg (if insomnia persists) (Switch to regular **ramelteon** from next day)
	Non-oral	None	**Hydroxyzine** (rescue)

Intervention period: The protocol-based intervention will be performed for 3 consecutive days from the date of enrollment (day 1 to day 3). Active PBPM group: Pharmacists will actively intervene to initiate prophylactic medications, regardless of the presence of symptoms. Passive PBPM group: Medications will be administered only as symptomatic treatment if insomnia or delirium symptoms are observed. Regular administration in the Passive group: If rescue medication is required for insomnia in the oral intake group, Ramelteon 8 mg will be switched to regular administration at 19:00 from the following day.・Blonanserin patch: In the Active PBPM (non-oral) group, the patch will be applied for 11 h (from 19:00 to 06:00 the following morning)

*Abbreviations*: *PBPM* Protocol-Based Pharmacotherapy Management; *eGFR* estimated glomerular filtration rate

**Fig. 1 Fig1:**
[figure not shown]
Detailed intervention and assessment schedules by enrollment timing. The timeline varies depending on the timing of enrollment. **A **Standard schedule: Enrollment on day 1 (08:30–17:00), with the 72-h protocol period starting that night. **B **Delayed schedule: Enrollment on day 2 for patients admitted at night or outside regular hours. The gray bar represents the 72-h protocol period. Blue squares indicate medication administration at 19:00 (Active group only). Green triangles indicate twice-daily nurse assessments using the DRS-R98-J at 20:00 and 10:00 (6 assessments total). The red star indicates the final diagnosis of the primary outcome by a blinded psychiatrist using DSM-5 criteria, performed within 3 days after protocol completion

Active PBPM group: Pharmacists will screen for delirium-inducing drugs upon admission. The patients will receive prophylactic medications for three consecutive nights.Oral intake possible: Ramelteon and lemborexant daily at 19:00.Oral intake impossible: The blonanserin patch will be applied daily from 19:00 to 06:00.Passive PBPM group: No prophylactic medications will be administered. Medications will be provided as rescue therapy only if insomnia occurs, following standard care procedures (Table 1).

### Criteria for discontinuing or modifying allocated intervention/comparator {15b}

Interventions will be discontinued in case of (1) intolerable adverse events, (2) use of prohibited medications, (3) withdrawal of consent, (4) post-enrollment discovery of ineligibility, or (5) significant clinical deterioration or death. No interim analysis is planned for this study. As such, no formal stopping rules for the entire trial have been established based on efficacy or futility. However, the principal investigator may terminate the trial early if unforeseen safety concerns arise.

### Strategies to improve adherence to intervention/comparator {15c}

Adherence to the study protocol is rigorously maintained through the structured PBPM framework. In this system, pharmacists proactively identify eligible patients and propose medication plans based on the pre-agreed protocol. These plans are then reviewed and formally approved by the attending physicians before any treatment is implemented. This collaborative verification process ensures that the intervention strictly adheres to the trial design. Furthermore, all prescriptions and administrations are recorded in the electronic medical record system, which is regularly reviewed by the research team to monitor and ensure full compliance with the protocol.

### Concomitant care permitted or prohibited during the trial {15d}

#### Standard care and concomitant management

All participants will receive standard non-pharmacological delirium prevention, including cognitive orientation, dehydration prevention, early mobilization, and sleep hygiene.Rescue medications: If agitation develops, rescue medications (e.g., intravenous hydroxyzine or haloperidol) will be administered according to a standardized treatment algorithm (Fig. 2).Prohibited medications: Concomitant use of other antipsychotics or hypnotics will be strictly prohibited during the study period.Adverse events: Any adverse events will be managed with appropriate supportive care. Detailed procedures for the systematic collection and classification of harms are described in the Harms {17} section. The participants will be covered by the clinical trial insurance.

**Fig. 2 Fig2:**
[figure not shown]
Standardized pharmacological management for agitation. Standardized pharmacological management flow when agitation develops during the study period

### Ancillary and post-trial care {34}

As mentioned in the Concomitant care section {15d}, participants are covered by clinical trial insurance for any study-related harm. After the 3-day study period, patients in the Active PBPM group will transition to the Passive PBPM protocol (standard management), while those in the Passive PBPM group will continue their current management. All other medical treatments and follow-up care will be provided at the discretion of the attending or sub-investigators based on the patients’ clinical needs.

### Outcomes {16}

The primary and secondary outcomes are defined below. Table 2 provides a detailed summary of all outcome measures, as specified in the SPIRIT 2025 statement, including domain, measure, metric, method of aggregation, and timing.

**Table 2 Tab2:** Detailed specification of outcome measures

Outcome	Domain	Measure	Specific Metric	Method of Aggregation	Timing
Primary	Delirium incidence	DSM-5 criteria	Binary (Yes/No)	Proportion (%)	Within 72 h
Secondary 1	Time-to- delirium onset	DSM-5 criteria	hours	The Kaplan–Meier method	Within 72 h
Secondary 2	Cumulative duration of delirium	DSM-5 criteria	hours	Mean (SD)	Within 72 h
Secondary 3	Peak Delirium severity	DRS-R98-J	Total/severity scores	Mean (SD)	Within 72 h
Secondary 4	Peak sleep–wake cycle	Item 1 of DRS-R98-J	Item score (0–3)	Mean (SD)	Within 72 h
Secondary 5	Rescue medication	Hydroxyzine (mg)	Cumulative dose	Mean (SD)	Within 72 h
Secondary 6	Agitation (Dementia)	Clinical assessment	Presence/absence	Proportion (%)	Within 72 h

### Primary outcome {16a}

The primary outcome will be the incidence of delirium within 3 days of the study initiation. Diagnosis will be established by an independent psychiatrist blinded to group allocation using the Diagnostic and Statistical Manual of Mental Disorders, 5th Edition (DSM-5) criteria. To ensure diagnostic accuracy, the psychiatrist will integrate the direct examination findings, nursing observations (including the DRS-R98-J scores), and baseline mental status reports from families.

### Harms {17}

#### Methods for collecting harms

Adverse events (AEs) will be collected systematically through daily clinical assessments and medical record reviews by the investigators from days 1 to 4. In addition to pre-specified harms, including hyperglycemia, extrapyramidal symptoms, falls, and oversedation, all unanticipated or unexpected harms will be identified through both daily bedside observations and spontaneous reporting by the nursing staff.

### Classification and grading

To ensure standardized reporting, all AEs will be classified using the Common Terminology Criteria for Adverse Events (CTCAE) version 5.0. The severity of each event will be graded on a scale from 1 (mild) to 5 (death). Safety will be also monitored through daily clinical laboratory tests (days 1–4), including complete blood count, blood chemistry (liver and renal function), and electrolytes, with results compared to baseline values obtained within 7 days before enrollment.

### Reporting and publication

All serious AEs occurring during the 7-day post-intervention period, as well as any event occurring after day 8 that is suspected to be causally related, will be reported to the Institutional Review Board (IRB) and the clinical trial insurance provider. In the final publication, all collected AEs, regardless of their suspected causal relationship to the intervention, will be presented in a summarized table to ensure full transparency of the safety profile of the PBPM.

### Participant timeline {18}

The schedule of enrollment, interventions, and assessments is summarized in Fig. 3.

**Fig. 3 Fig3:**
[figure not shown]
Schedule of enrollment, interventions, and assessments. (a) Recommended content can be displayed using various schematic formats. (b) Time points: −t1 to 0: Enrollment phase; 0: day 1 (initiation of PBPM); t1: day 2; t2: day 3; t3: day 4 morning (end of intervention); tx: day 7 (final follow-up). (c) Arrows indicate continuous delivery of PBPM or standard care. (d) Laboratory tests are performed at least once between day 1 and Day 4. (e) DRS-R98-J: Conducted by trained nurses twice daily (10:00 and 20:00), except day 1 (evening only) and day 4 (morning only). Time window is ±30 min. (f) Agitation is monitored continuously through nursing logs. (g) DSM-5 Diagnosis: Established by a blinded psychiatrist between day 4 and Day 7

### Sample size {19}

The sample size was determined on the basis of previous studies that investigated delirium prevention using orexin receptor antagonists and melatonin receptor agonists [8, 18]. One study reported a delirium incidence rate of 20.5% in the standard administration group (equivalent to the Passive PBPM group) compared with 7.4% in the early administration group (equivalent to the Active PBPM group). Another randomized controlled trial reported delirium rates of 16.7% and 0% in the placebo and suvorexant groups, respectively.

In this study, we anticipate a higher baseline incidence because the criteria include patients with nil per os status. Therefore, we estimated the incidence rates of delirium within 3 days of admission to be 25% in the Passive PBPM group and 5% in the Active PBPM group. To detect this difference with 80% power at a two-sided significance level of 5% (*α* = 0.05) using Newcombe’s method for the difference in proportions, 96 patients will be required. Accounting for a projected dropout rate of 10%, the target sample size will be set at 105 patients.

### Recruitment {20}

To ensure the target sample size is achieved within the study period, several proactive strategies have been implemented:Expansion of Eligibility and Timing: To maximize the recruitment rate, the protocol was amended to expand enrollment days to include weekends and public holidays. Additionally, the enrollment window was extended from the day of admission (day 1) to the following day (day 2) to capture patients admitted at night or outside regular working hours. (details are provided in Section {31}).Multi-professional Collaboration: The study is conducted through a collaborative effort involving emergency physicians, psychiatrists, pharmacists, and nurses. This team-based approach ensures a 24/7 screening capability and prevents the missing of potential candidates.Pharmacist-led Screening: Pharmacists screen all new admissions to the emergency ward daily, utilizing the hospital’s electronic medical record system to identify eligible patients aged 65 years or older.Ongoing Staff Education: Periodic briefing sessions are provided to the nursing and medical staff to maintain awareness of the study and ensure adherence to the revised enrollment procedures.

## Assignment of interventions: randomization

### Sequence generation: who will generate the sequence {21a}

The randomization sequence will be generated by an independent data center (Department of Clinical Trial Science, iACT, Kyoto University Hospital) using the minimization method. This study will use a Prospective Randomized Open-label Blinded Endpoint design.

### Sequence generation: type of randomization {21b}

Participants will be randomly assigned in a 1:1 ratio to either the Active or Passive PBPM group (Fig. 4). Stratification factors will include age (<75 vs. ≥75 years) and the baseline use of high-risk drugs for delirium.

**Fig. 4 Fig4:**
[figure not shown]
Study flowchart. The participants will be randomized into the Active or Passive PBPM group. In the Active PBPM group, prophylactic medications will be administered based on the ability to take oral intake. In the Passive PBPM group, medications will be administered only when insomnia occurs

### Allocation concealment mechanism {22}

Selection bias will be minimized using a sequentially numbered allocation list. After obtaining written informed consent and confirming eligibility, the investigators will reveal the allocation by opening the opaque, tamper-evident seals.

### Implementation {23}

The enrollment and assignment procedures will be conducted as follows to ensure strict adherence to the protocol:Enrollment: Emergency physicians will screen eligible patients and obtain written informed consent.Assignment: After confirming eligibility, the ward physician (or the ward physician in collaboration with the ward pharmacist) will open the next sequentially numbered, opaque, tamper-evident seal to reveal the group assignment.Communication and Initiation: The assignment results will be shared among the ward physicians, nurses, and pharmacists. Based on the revealed group (Active or Passive PBPM), the ward physician and pharmacist will initiate the intervention by providing medical orders to the nurses. The ward nurses will then administer the medications or apply the patches to the patient according to these orders. The personnel responsible for the initial enrollment (emergency physicians) will not have access to the allocation sequence in advance, and the assignment will remain concealed until the point of opening the seal.

### Assignment of interventions: blinding

#### Who will be blinded {24a}

Owing to the nature of the pharmacological intervention, the patients and ward staff will not be blinded. However, the psychiatrists responsible for the definitive diagnosis of delirium (the primary outcome) will be strictly blinded to the group allocation to prevent detection bias.

### How will be blinding be achieved {24b}

As this study evaluates a pharmacological management protocol involving different administration timings (prophylactic vs. symptomatic), it is conducted as an open-label trial, and no placebo will be used. Therefore, the ward physicians, pharmacists, and nurses will not be blinded to the group assignment. However, to minimize detection bias, the primary outcome (diagnosis of delirium based on DSM-5 criteria) will be assessed by psychiatrists who are not involved in the participants’ daily care or the PBPM intervention. The group assignment is not formally disclosed to these psychiatrists, and they establish the diagnosis as independent evaluators based on the clinical records. This approach follows the PROBE (Prospective Randomized Open-label Blinded Endpoint) design.

### Procedure for unblinding if needed {24c}

Not applicable. This is an open-label trial in which ward physicians, pharmacists, and nurses are aware of the group assignment from the time of enrollment. Therefore, no specific procedure for unblinding is required in the event of an emergency, as the intervention details are already known to the clinical staff responsible for the participant’s safety.

## Data collection and management

### Plans for assessment and collection of outcomes {25a}

Data will be collected and managed to ensure high quality and reliability through the following plans:Clinical Assessment Tools: The primary and secondary outcomes will be assessed using the DRS-R98-J, a validated Japanese version of a widely used tool for evaluating delirium severity and diagnosis with high inter-rater reliability.Training of Assessors: Before study initiation, all participating nurses will receive standardized training on the use of the DRS-R98-J to minimize inter-observer variability. The psychiatrists responsible for the final diagnosis are experts in delirium management and follow the DSM-5 criteria.Data Collection and Quality Assurance: Data will be initially recorded in the electronic medical records and then transcribed into paper-based case report forms (CRFs) by the investigators. The principal investigator will ensure the completeness and accuracy of all entries. To maintain data integrity, a double-check against source documents will be performed, and any corrections to the CRFs will be documented according to standardized procedures.

### Plans to promote participant retention and complete follow-up {25b}

Given the acute nature of the setting and the short follow-up period (72 h), high participant retention is expected. To ensure complete follow-up and minimize bias, the following strategies will be employed:

Retention Strategies: The PBPM intervention and assessments will be integrated into the standard clinical workflow of the emergency ward to minimize the burden on participants. Investigators and ward staff will monitor the participants’ clinical status daily to ensure adherence to the protocol.Data Collection for Discontinued Participants: If a participant deviates from or discontinues the intervention protocol (e.g., due to medical necessity, adverse events, or transfer to another ward), every effort will be made to continue the outcome assessments until the 72-h endpoint, provided that consent is not withdrawn.Outcome Data for Deviations: For participants who discontinue the study, the following data will be collected up to the point of discontinuation and included in the intention-to-treat (ITT) analysis:DRS-R98-JIncidence of agitation and medication recordsFinal delirium diagnosis by a psychiatrist (if possible, based on records up to the time of discontinuation)Withdrawal of Consent: If consent is withdrawn by the participant or their representative, all further data collection will cease. Data collected up to that point will be handled in accordance with the ethical approval and the participant’s preference.

### Data management {26}

Data management will be performed by [name] (TT). On-site monitoring will be conducted annually by [name] (YO) to ensure data integrity and protocol compliance. Although both are affiliated with the Department of Primary Care and Emergency Medicine at Kyoto University Hospital, they are strictly independent of the study execution team and will not be involved in patient enrollment, allocation, or clinical assessment. This oversight structure ensures objective quality control and rigorous adherence to the study protocol.

### Confidentiality {33}

Access to the raw data will be restricted to authorized study personnel only. All data will be maintained in accordance with the CRA and the study protocol.

## Statistical methods

### Statistical methods for primary and secondary outcomes {27a}

The primary analysis will be performed on the FAS and repeated on the PPS as a sensitivity analysis. The incidence of delirium diagnosed using the DSM-5 within 3 days will be calculated for each group, with 95% confidence intervals (CIs). The between-group difference in incidence (Active PBPM minus Passive PBPM) and its 95% CI will be estimated using Newcombe’s method. Statistical significance will be set at a two-sided level of 5%. If the upper limit of the 95% CI for the difference is <0, the Active PBPM group will be considered to have a significantly lower incidence of delirium.

Unless otherwise specified, following secondary analyses will use a two-sided significance level of 5% and 95% CIs.Time to delirium: The time from enrollment to the onset of delirium (DSM-5) will be analyzed using Kaplan–Meier curves, with observations censored at 72 h.Delirium severity and sleep–wake cycle: Summary statistics for the worst DRS-R98-J severity scores and item 1 (sleep–wake cycle disturbance) scores recorded while the patient was awake will be compared between groups.

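### Allocation is minimised on two factors that the primary risk difference then ignores: a valid analysis, but mildly conservative if those factors predict delirium

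*Protocol article*

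**What the plan says.** Section {21a} of the protocol article states that the sequence is generated "using the minimization method". Section {21b} gives the ratio and the factors: "Participants will be randomly assigned in a 1:1 ratio to either the Active or Passive PBPM group", and "Stratification factors will include age (<75 vs. ≥75 years) and the baseline use of high-risk drugs for delirium".

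Section {27a} fixes the primary analysis: "The between-group difference in incidence (Active PBPM minus Passive PBPM) and its 95% CI will be estimated using" Newcombe's method. Superiority is declared by the rule "If the upper limit of the 95% CI for the difference is <0". Neither allocation factor enters this analysis or its per-protocol repeat. Section {27c} adds only a worst-case imputation, and section {27d} names no adjusted primary analysis.

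Section {19} sizes the trial with the same unadjusted Newcombe method, assuming "25% in the Passive PBPM group and 5% in the Active PBPM group", and arrives at 96 patients before dropout.

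Section {5} states that the detailed statistical analysis plan is integrated in this protocol and refers to the statistical methods section. The unadjusted interval is therefore the stated primary rule.

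**The concern.** Balancing allocation on a factor that predicts outcome removes the between-stratum part of the variation from the treatment comparison. A crude two-sample interval still counts that part. It is then wider than it needs to be, its coverage exceeds 95%, and some power goes unused. A crude difference also cannot correct any imbalance left in the two factors. Some may remain, because the full analysis set in section {27b} drops participants after allocation.

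Few events are expected: 48 × 0.25 + 48 × 0.05 = 12 + 2.4 = 14.4. Both factors must be known to run the minimisation, so using them in the analysis needs no new data.

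**Working it through.** **Inputs from the protocol article.** Rates 25% and 5%, 80% power, two-sided 5%, 96 patients (section {19}); 1:1 minimisation on two binary factors (sections {21a} and {21b}); Newcombe interval, success if the upper limit is below 0 (section {27a}).

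**Assumptions not in the document.** 60% aged ≥75, 50% on high-risk drugs, a biased coin of 0.8 in the minimisation, and an odds ratio of 1 to 4 for each factor.

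**Step 1: the plan's own figure.** Exact binomial enumeration of the chance that the upper Newcombe limit (Wilson limits, no continuity correction) falls below 0 gives:
- 47 per arm: 79.3%
- 48 per arm: 80.3%

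The stated 96 is reproduced for the unadjusted analysis. The usual pooled formula gives 49 per arm (98 in total), which is close.

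**Step 2: what stratification could save, large-sample.** The per-patient variance term of the crude difference is 0.25 × 0.75 + 0.05 × 0.95 = 0.1875 + 0.0475 = 0.2350. Stratification replaces each p(1−p) by its average within the four strata.

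Example, odds ratio 3 per factor. The stratum weights are 0.2, 0.3, 0.2, 0.3, and the Passive risks are 0.080, 0.206, 0.206, 0.437. The within-stratum Passive term is 0.2 × 0.080 × 0.920 + 0.3 × 0.206 × 0.794 + 0.2 × 0.206 × 0.794 + 0.3 × 0.437 × 0.563 = 0.170, against 0.1875 crude. With the Active arm included, the variance ratio is 0.9215.

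| Odds ratio per factor | Variance ratio | Width ratio (square root) | Patients equivalent to 96 (96 × variance ratio) |
|---|---|---|---|
| 1 | 1.000 | 1.000 | 96 |
| 1.5 | 0.9877 | 0.994 | 94.8 |
| 2 | 0.9658 | 0.983 | 92.7 |
| 3 | 0.9215 | 0.960 | 88.5 |

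**Step 3: simulation of the trial as designed.** N = 96 with minimisation as above, 40,000 runs per setting. Error and coverage are at equal rates of 25%; power is at 25% vs 5%. The last column compares crude Newcombe with a Mantel-Haenszel difference and a score-type interval.

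| Odds ratio per factor | Crude one-sided error | Crude coverage | Crude power | Power gain, stratified score-type |
|---|---|---|---|---|
| 1 | 2.4% | 95.1% | 80.9% | about 0 |
| 2 | 2.3% | 95.5% | 81.3% | 0.6 points |
| 3 | 2.1% | 96.0% | 81.7% | 1.3 points |
| 4 | 1.75% | 96.4% | 82.1% | 2.1 points |

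Arm sizes vary a little under minimisation, so crude power at odds ratio 1 is not exactly the 80.3% of step 1. A separate set of 200,000 runs gave crude one-sided errors of 2.5%, 2.3% and 2.0% at odds ratios 1, 2 and 3.

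**Step 4: which stratified interval.** The choice matters more than the stratification.
- Mantel-Haenszel with the plain Sato variance (Wald-type): one-sided error 2.6 to 2.8%, coverage about 94.5%. Its power is 83.1% even at odds ratio 1, where there is nothing to recover, so about 2 points of its apparent gain come from the interval type.
- A stratified Newcombe form: recovered nothing.
- Mantel-Haenszel with a score-type interval: one-sided error 2.2 to 2.35%, gains as tabulated.

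**The case against.** The strongest reply is that nothing here is an error. Section {19} sizes the trial with the method that section {27a} uses, so design and analysis agree, and the crude analysis delivers the planned power at 96. Crude analysis after minimisation is conservative, so it adds no false-positive risk. All of this stands.

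The reply continues that the loss depends on inputs the protocol does not give. This also stands. Section {14a} requires at least one of six risk factors, and delirium-inducing drug use is one of them, so every non-user must carry another. That may weaken the contrast this factor provides. At odds ratio 1 there is no loss.

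Third, a Wald-type stratified interval would replace one that holds its level with one that slightly exceeds it: two-sided error was 5.5 to 5.7% at equal rates of 25%. This stands against that interval, but not against stratification, because the score-type version kept its level.

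Finally, adjusted analyses are often left to a separate analysis plan. For supplementary analyses that is fair. The primary rule, however, is written out in section {27a}, and section {5} says the analysis plan is contained in this protocol.

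**Conclusion.** The mismatch is real and its consequence is small. The primary analysis leaves out both factors used to balance allocation. The crude interval stays valid; it is mildly conservative only if those factors predict delirium. For odds ratios of 1 to 4 per factor, one-sided error runs from 2.4% down to about 1.75%, coverage from 95.1% up to 96.4%, and the power forgone is about 0 to 2 points. These figures rest on the assumed prevalences, coin and odds ratios. The direction does not.

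A reader might infer three stronger things that the document does not support:
- **That the interval is certainly too wide.** This needs a prognostic strength that is nowhere stated.
- **That the trial falls short of its planned power because it does not adjust.** It does not: 96 was derived for the unadjusted interval and gives 80.3%.
- **That the false-positive rate is inflated.** The effect runs the other way.

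The change is worth making because it costs almost nothing, not because the present analysis would mislead.

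**What to change.** In section {27a}, before data lock, define the primary estimate as the Mantel-Haenszel risk difference stratified by age (<75, ≥75) and baseline high-risk drug use. Give it a score-type 95% interval with the formula named, since the gain and the level depend on the form chosen. Keep the rule that the upper limit must be below 0. Do not use the plain Sato-Wald interval. Keep crude Newcombe as the supporting analysis.

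Do not add a fallback to a logistic model when strata are judged too sparse. With about 2.4 events expected in the Active arm over four strata, sparseness is the likely case, and a switch without a defined trigger makes the primary method depend on the data.

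The cost is a wording amendment and slightly more analysis work. No new data and no change in sample size are needed. If the factors turn out not to be prognostic, little or nothing is gained. The trial status section describes recruitment as ongoing, so pre-specification was still possible at that point.
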